### Sample Size

We planned to include up to 40 patients and to determine the final sample size after evaluating the results of the first twenty patients included in the trial in regard to the MCID of the primary outcome (change in WMFT, Functional Ability Scale at 6 weeks compared to baseline).

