## Abstract

**Background:** Repetitive peripheral nerve sensory stimulation (RPSS) has emerged as a potential adjuvant strategy to motor training in stroke rehabilitation. The aim of this study is to test the hypothesis that 3 h sessions of active RPSS associated with functional electrical stimulation (FES) and task-specific training (TST) distributed three times a week, over 6 weeks, is more beneficial to improve upper limb motor function than sham RPSS in addition to FES and TST, in subjects with moderate to severe hand motor impairments in the chronic phase (>6 months) after stroke.

**Methods:** In this single-center, randomized, placebo controlled, parallel-group, double-blind study we compare the effects of 18 sessions of active and sham RPSS as add-on interventions to FES and task-specific training of the paretic upper limb, in 40 subjects in the chronic phase after ischemic or hemorrhagic stroke, with Fugl-Meyer upper limb scores ranging from 7 to 50 and able to voluntarily activate any active range of wrist extension. The primary outcome measure is the Wolf Motor Function Test (WMFT) after 6 weeks of treatment. The secondary outcomes are the WMFT at 3, 10, and 18 weeks after beginning of treatment, as well as the following outcomes measured at 3, 6, 10, and 18 weeks: Motor Activity Log; active range of motion of wrist extension and flexion; grasp and pinch strength in the paretic and non-paretic sides (the order of testing is randomized within and across subjects); Modified Ashworth Scale; Fugl-Meyer Assessment-Upper Limb in the paretic arm; Barthel Index; Stroke Impact Scale.

**Discussion:** This project represents a major step in developing a rehabilitation strategy with potential to have impact on the treatment of stroke patients with poor motor recovery in developing countries worldwide. The study preliminarily evaluates a straightforward, non-invasive, inexpensive intervention. If feasibility and preliminary efficacy are demonstrated, further investigations of the proposed intervention (underlying mechanisms/ effects in larger numbers of patients) should be performed.

**Trial Registration:** NCT02658578.

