### Randomization, Allocation Concealment and Blinding

Subjects are randomized by the Principal Investigator (PI) with a basic random number computerized generator (randomization.com) in blocks of four, to active or sham RPSS in a 1:1 ratio. The randomization schedule is concealed in a locked cabinet accessed only by the PI and the investigators who administer RPSS.

Participants and investigators who assess outcomes are blinded to the interventions performed. Subjects are blinded to the experimental hypothesis and are not allowed to discuss their experience during the interventions with the researchers involved in assessment of outcomes or with other subjects. The clinical research forms of the blinded intervention are kept concealed in a locked cabinet. After each intervention session, subjects are asked: do you think your nerves were stimulated (yes/no)? Do you think your hand is different (worse/better/no change)?

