### Outcome Measures

The primary outcome measure is the Wolf Motor Function Test (WMFT) (40) after 6 weeks of treatment (end of treatment). The average time to perform 15 functional tasks (maximum, 120 s per task; if >120 s, the score is 121 s) as well as the quality of movement (Functional Ability Scale; range, 0 to 5) are assessed. The Minimal Clinically Important Differences (MCID) in the chronic phase are 1.2 to 2 s for the average time to complete the tasks, and 0.2 to 0.4 points for the Functional Ability Scale (41). The WMFT is a valid instrument with high interrater and test-retest reliabilities, as well as high internal consistency (42). The original version of the WMFT was developed to assess the effects of CIMT in stroke and traumatic brain injury.

The secondary outcomes are the WMFT at 3, 10 and 18 weeks after beginning of treatment, as well as the following outcomes measured at 3, 6, 10, and 18 weeks after beginning of treatment: MAL; active range of motion (ROM) of wrist extension and flexion; grasp and pinch strength in the paretic and non-paretic sides (the order of testing is randomized within and across subjects); MAS; FMA-UL in the paretic arm; BI; SIS; Beck Depression Inventory Short Form. Measurements assessed after 3 and 6 weeks of treatment are scheduled for days other than those in which the patients receive treatment, in order to avoid fatigue.

In addition, ROM of wrist extension and flexion is measured before and after the first session of treatment. ROM of wrist extension and flexion is measured with an analogic goniometer (ISP® Instituto São Paulo, São Paulo, Brazil) (43). Averages of three trials are calculated. Grip strength is measured with a Jamar dynamometer (Saehan Jamar, Changwong Korea) and pinch strength, with a digital dynamometer (Kratos, São Paulo, Brazil) (44). The trunk and the arms are stabilized and the wrist is kept in a neutral position during measurements.

All outcomes are evaluated by trained researchers blinded to the type of RPSS administered to patients. Assessments are videotaped.

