### Data Analysis

Analysis of variance with repeated measures or generalized estimating equations models with factors GROUP (active or sham) and TIME (baseline, 3, 6 weeks) will be performed, according to the distribution of the data. After all follow-ups have been completed, analyses will be performed with factors GROUP (active or sham) and TIME (baseline, 3, 6, 10, and 18 weeks). If there is an imbalance in Fugl-Meyer scores between the groups, then the analysis will be adjusted for baseline severity.

Also, the percentages of patients in the active and sham groups who will attain gains equal or larger than MCID in the WMFT and MAL, FMA-UL at 6, 10, and 18 weeks will be compared with chi-square tests or Fisher's exact tests.

Compliance with the interventions will be compared in the active and sham groups with Mann–Whitney tests.

Intention-to-treat (ITT) and per-protocol analyses will be performed. For intention-to-treat analysis, missing observations will be imputed with the Last Observation Carried Forward (LOCF).

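### The final sample size follows a look at the first 20 patients' primary-outcome results, with no stated rule, blinding or adjustment, so type I error is not shown to be controlled

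*Protocol article*

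**What the plan says.** The whole of the Sample Size section is one sentence. It sets a ceiling ("We planned to include up to 40 patients") and says the investigators will "determine the final sample size after evaluating the results of the first twenty patients included in the trial". The yardstick for that evaluation is given as "in regard to the MCID of the primary outcome (change in WMFT, Functional Ability Scale at 6 weeks compared to baseline".

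Three other places bear on it:

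- The Abstract describes the trial as conducted "in 40 subjects in the chronic phase after ischemic or hemorrhagic stroke", with no mention that the number may change.
- Outcome Measures gives the MCID as a range, "0.2 to 0.4 points for the Functional Ability Scale", not a single value.
- Randomization, Allocation Concealment and Blinding assigns patients "in blocks of four, to active or sham RPSS in a 1:1 ratio" and keeps the schedule in a cabinet "accessed only by the PI and the investigators who administer RPSS". Participants and outcome assessors are blinded. Nothing is said about who makes the look at 20 patients or in what form they see the data.

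Data Analysis names the main models ("Analysis of variance with repeated measures or generalized estimating equations models with factors GROUP (active or sham) and TIME (baseline, 3, 6 weeks") and mentions no allowance for the look.

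**The concern.** A sample size that depends on observed efficacy is an interim analysis, whatever it is called. If arms are compared at 20 patients and a good result can end recruitment there, the trial has two chances to be positive. An ordinary 5% test then no longer has a 5% false-positive rate, and trials that end early tend to do so on a lucky high estimate.

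The article states that the size will follow the results, so this is more than a detail left for later. It leaves open the features that decide whether harm follows: by arm or pooled, which result leads to which size, and which value in a two-fold MCID range applies. The abstract and introduction present the trial as a test of active against sham stimulation, and the Discussion makes further work conditional on preliminary efficacy. A false or inflated positive would therefore misdirect the next step.

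**Working it through.** **Reproducing the plan's figure.** The 40 cannot be reproduced: the section gives no significance level, power, SD or dropout.

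**Inputs from the article.** Maximum 40; look at 20; 1:1 in blocks of four, so 20 patients are five complete blocks, 10 per arm; MCID 0.2 to 0.4 points.

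**Assumptions.** Two-sided 5%; SD of change 0.3 to 0.8 points; no dropout; a simple two-sample comparison of change at 6 weeks in place of the repeated-measures model.

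**1. Stop at 20 if p<0.05, otherwise continue to 40.** The two test statistics have correlation √(20/40) = 0.707. Type I error = 1 − P(|Z₁|<1.96 and |Z₂|<1.96) = 0.083. With t-tests, simulation gives 0.084.

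**2. Worst case.** For each interim value z₁, choose the final N from 20 to 40 that maximises the conditional chance of rejection, then average over z₁ under the null: 0.086.

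**3. Other rules the sentence could mean** (simulated with t-tests, no true effect):

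| Rule at 20 patients | Type I error |
|---|---|
| Pooled mean change, or blinded SD only | 5.0–5.1% |
| Stop only if the between-arm difference is below the MCID | 3.9–5.0% |
| Stop if the difference in favour of active reaches the MCID | 5.1–6.1% |
| Stop if it reaches the MCID and p<0.05 | 5.1–6.7% |
| Recompute N from the observed effect, capped at 40 | 6.1–6.2% |

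Ranges run over MCID 0.2 or 0.4 and the assumed SDs. If a difference of 0.4 in either direction ended recruitment, the figure at SD 0.5 would be 7.3%.

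**4. Bias.** Suppose recruitment ends at 20 when the observed difference is at least c, and otherwise goes to 40. The average bias is ½·SE·φ((c − δ)/SE), where δ is the true difference, φ the standard normal density and SE = SD·√(2/10).

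- δ = 0.3, SD 0.3, c = 0.2: SE = 0.134; ½ × 0.134 × 0.302 = +0.02.
- δ = 0.3, SD 0.8, c = 0.2: SE = 0.358; ½ × 0.358 × 0.384 = +0.07.
- If recruitment instead ends only when the difference is below c, the sign reverses: −0.02 to −0.07.
- For a look at the pooled mean the bias is about 0.

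Among only those trials that stop, the exaggeration is larger. With δ = 0.2, SD 0.4 and c = 0.4, SE = 0.179 and (0.4 − 0.2)/0.179 = 1.118. The chance of stopping is 0.13, and the mean estimate given stopping is 0.2 + 0.179 × 0.2135/0.1318 = 0.49. Over all trials in that scenario the bias is ½ × 0.179 × 0.2135 = +0.02.

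**5. How much 20 patients can say.** The 95% half-width for the between-arm difference is t(0.975, 18)·SD·√(2/10) = 2.101 × 0.447 × SD: 0.28 at SD 0.3, 0.38 at 0.4, 0.56 at 0.6. These widths are comparable with or larger than the MCID itself.

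**6. Why one MCID value matters.** At SD 0.4 and 80% power, n per arm ≈ 2(1.96 + 0.84)²(0.4/Δ)² plus about one for the t-distribution: 64 for Δ = 0.2, 17 for Δ = 0.4. The cap of 40 in total limits the actual choice, but which end of the range applies still decides whether the cap binds.

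**The case against.** A reader might infer that the type I error does exceed 5% and that the estimate is biased upward. The article does not support that. Its yardstick is change from baseline, and the sentence mentions no between-arm comparison. Data Analysis also uses the MCID as a per-patient gain threshold, so the look could be a responder count or a pooled mean change. A pooled look costs essentially nothing in error or bias, and stopping only on a poor result lowers the error and biases the estimate downward. The 8.3% needs a p-value rule the article never mentions, and 8.6% is a bound over every possible choice of size. The 0.49 estimate concerns only the roughly 13% of trials that stop in one assumed scenario. All of this stands, and it limits the claim.

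The principal investigator's access to the schedule shows that an unblinded look is possible. It does not show that one was planned or made.

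It can also be said that an analysis plan not shown may contain an adjustment, and that the trial calls itself preliminary. The first is fair as to test details and the significance level. It does not remove the point that the article itself ties the size to results. The second does not remove the hypothesis test stated in the abstract and introduction.

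The pooled reading has its own weakness: pooled change from baseline says little about the size needed to compare active with sham.

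**Conclusion.** The concern holds in a limited form. The article commits to a results-driven sample size without the features needed to judge its effect on the primary test, and its 40 in the abstract does not match the ceiling of 40 in the Sample Size section. Error control is not shown, which is different from being shown to fail. Under the arm-level MCID stopping rule closest to the text, the excess is at most about one percentage point; the ceiling over any choice of size is about 8.6%. Average bias is a few hundredths of a point, and its direction depends on which results can end recruitment. These figures rest on an assumed two-sided 5% level, assumed SDs of 0.3 to 0.8, no dropout, and a simple two-group comparison.

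**What to change.** Set the final size at 40 (20 per arm) in the Sample Size section, in agreement with the abstract, and state that it does not depend on between-arm results. With the size fixed, no look at 20 patients is needed for sizing.

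If the size is to stay adjustable, base it only on the blinded pooled SD of change in the Functional Ability Scale, with one MCID value named in advance and the rule from SD to size written out. Simulated type I error for that approach is 5.0%.

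If an arm-level look is wanted, or has already happened (the Discussion says enrolment had begun), disclose it: who looked, at what, and what was decided. Then test at O'Brien-Fleming limits, p<0.0052 at 20 patients and p<0.0480 at 40, which hold the overall two-sided level at 5% for looks at those two points. Alternatively, use an inverse-normal combination of the two stages. Report an estimate that allows for the look.

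The cost is a sentence or two in the protocol or analysis plan, and the loss of the option to end at 20 on an unadjusted result. Forty is already the planned maximum. If an arm-level look has already taken place, the disclosure and adjusted analysis are additional work. Fixing the size does not by itself make 40 adequate for a difference of 0.2 points; that is a separate question.

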### Data Analysis

Analysis of variance with repeated measures or generalized estimating equations models with factors GROUP (active or sham) and TIME (baseline, 3, 6 weeks) will be performed, according to the distribution of the data. After all follow-ups have been completed, analyses will be performed with factors GROUP (active or sham) and TIME (baseline, 3, 6, 10, and 18 weeks). If there is an imbalance in Fugl-Meyer scores between the groups, then the analysis will be adjusted for baseline severity.

Also, the percentages of patients in the active and sham groups who will attain gains equal or larger than MCID in the WMFT and MAL, FMA-UL at 6, 10, and 18 weeks will be compared with chi-square tests or Fisher's exact tests.

Compliance with the interventions will be compared in the active and sham groups with Mann–Whitney tests.

Intention-to-treat (ITT) and per-protocol analyses will be performed. For intention-to-treat analysis, missing observations will be imputed with the Last Observation Carried Forward (LOCF).

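### The plan designates no baseline-adjusted week-6 contrast as the primary test, and the omnibus GROUP x TIME test its factors lead to is a less specific and usually less powerful substitute

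*Protocol article*

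**What the plan says.** Outcome Measures sets the endpoint: "The primary outcome measure is the Wolf Motor Function Test (WMFT) (40) after 6 weeks of treatment (end of treatment". The Sample Size section narrows it to "change in WMFT, Functional Ability Scale at 6 weeks compared to baseline".

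Data Analysis then plans "Analysis of variance with repeated measures or generalized estimating equations models with factors GROUP (active or sham) and TIME (baseline, 3, 6 weeks". These models "will be performed, according to the distribution of the data", with no criterion for choosing between them. Once follow-up is complete, further "analyses will be performed with factors GROUP (active or sham) and TIME (baseline, 3, 6, 10, and 18 weeks".

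The section names no interaction term and no week-6 contrast. Adjustment for baseline severity is conditional on a Fugl-Meyer imbalance; adjustment for baseline WMFT is not mentioned. For intention-to-treat, missing values are carried forward, so every patient has a value at every visit. The same section also compares the percentages of patients reaching the MCID at 6, 10 and 18 weeks.

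On size: "We planned to include up to 40 patients and to determine the final sample size after evaluating the results of the first twenty patients", allocated "in blocks of four, to active or sham RPSS in a 1:1 ratio".

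**The concern.** With GROUP and TIME as factors and baseline as a TIME level, standard output gives a GROUP main effect and an omnibus GROUP x TIME test. The main effect averages in a pre-treatment visit where randomisation leaves no true difference. The omnibus test responds to any departure from parallel profiles (2 df with three visits, 4 df with five). Neither is the week-6 comparison.

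Unless the deciding contrast is fixed, a significant interaction driven by another visit could be read as success on the primary endpoint, or a real week-6 effect could be missed. The baseline value of the outcome, usually the strongest predictor of the week-6 value, is also not used as a covariate. Finally, the data choose between two methods that need not have the same error rate in a sample this small.

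**Working it through.** **Inputs from the article.** At most 40 patients, 1:1, so n = 20 per arm; a look after 20 patients (10 per arm). Three TIME levels, later five. MCID "0.2 to 0.4 points for the Functional Ability Scale".

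**Assumed, because the article does not give them.** Two-sided alpha 0.05, SD σ = 1 (effects in SD units), equal correlation ρ between visits (0.7 unless stated), a 0.7 SD effect in the patterns below, no dropout. The plan's figure of 40 cannot be reproduced, since it comes without alpha, power, SD or target difference.

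Closed forms are set beside simulation (10,000 trials per null setting, 4,000 per effect setting).

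**1. What each term tests.** Let δ0, δ3, δ6 be the true group differences, with δ0 = 0 by randomisation.
- GROUP: (δ0 + δ3 + δ6)/3.
- GROUP x TIME: whether δ0 = δ3 = δ6.
- Week-6 change contrast: δ6 − δ0.
- Week-6 ANCOVA: δ6 given the baseline value.

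**2. Significance without a week-6 effect.** For the RM-ANOVA interaction, λ = (n/2) Σ(δt − mean δ)² / [σ²(1 − ρ)].
- Three visits, δ = (0, 0.7, 0): mean 0.2333; Σ = 0.49 − 3 × 0.2333² = 0.3267; λ = 10 × 0.3267/0.3 = 10.89 on 2 and 76 df. Rejection 83.4% (simulated 83.3%). Simulated week-6 ANCOVA: 4.6%.
- Five visits, δ = (0, 0, 0, 0.5, 0.7): mean 0.24; Σ = 0.74 − 5 × 0.24² = 0.452; λ = 15.07 on 4 and 152 df. Rejection 88.2% (simulated 88.7%). Simulated week-6 ANCOVA: 5.2%.

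**3. Power for a real week-6 effect, δ = (0, 0.35, 0.7), 20 per arm.** The per-patient variance is 2σ²(1 − ρ) for change and σ²(1 − ρ²) for ANCOVA, a ratio of 2/(1 + ρ): 1.33, 1.18 and 1.05 at ρ = 0.5, 0.7 and 0.9. Simulated power:

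| ρ | Omnibus interaction (RM-ANOVA) | Week-6 change contrast (t test) | Week-6 ANCOVA |
|---|---|---|---|
| 0.5 | 48.1% | 57.9% | 69.1% |
| 0.7 | 71.5% | 79.5% | 83.9% |
| 0.9 | 99.4% | 99.7% | 99.8% |

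Closed form at ρ = 0.7:
- Interaction: λ = 10 × 0.245/0.3 = 8.17, power 70.9%.
- Change: SE = √(0.1 × 0.6) = 0.245, power 79.5%.
- ANCOVA: SE = √(0.1 × 0.51) = 0.226, power 85.5%. This is slightly optimistic because it ignores estimation of the slope.

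The gap depends on the pattern. If the effect appears only at week 6, the omnibus test has 60.4% against 68.4% for ANCOVA at ρ = 0.5, and 82.1% against 83.8% at ρ = 0.7.

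**4. Type I error of uncorrected GEE.** With complete balanced data and a saturated GROUP x TIME mean, the uncorrected sandwich variance is the usual variance times (n − 1)/n.
- Week-6 change contrast, z reference: reject if |t| > 1.96 × √((n − 1)/n). For n = 20, 1.910 on 38 df: 6.4% (simulated 6.3%). For n = 10, 1.859 on 18 df: 7.9% (simulated 8.0%).
- Omnibus test, three visits, chi-square reference: reject if Hotelling T² > 5.991 × (n − 1)/n. For n = 20, T² = 5.692, F = 5.692 × 37/(38 × 2) = 2.771 on 2 and 37 df: 7.6% (simulated 8.0%). For n = 10, T² = 5.392, F = 5.392 × 17/(18 × 2) = 2.546 on 2 and 17 df: 10.8% (simulated 11.1%).
- Five visits, simulated: 9.9% at 40 patients and 18.3% at 20.
- Skewed (lognormal) data, three visits, simulated: contrast 5.6% at 40 patients and 6.8% at 20; omnibus 6.5% and 9.3%.

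For comparison, with normal data the RM-ANOVA interaction without sphericity correction stays at 4.8% to 5.3%. The t test on change, which equals the contrast with the n/(n − 1) correction and a t reference, is at 5.0% with 40 patients and 5.2% with 20.

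**The case against.** The strongest reply is that the model contains what is needed. Week 6 is a TIME level, and the Sample Size section words the endpoint as change from baseline, which is exactly the GROUP by (week 6 minus baseline) contrast. That contrast has correct size when computed with a t reference. A reader might infer that the plan cannot test week 6 at all; the article does not support that, and the MCID responder comparison also covers week 6. That comparison is dichotomised, is repeated over times and scales, and is not named as primary, so it does not settle which result decides the trial.

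A reader might also take the GROUP main effect as the primary test and quote its low power: 22.8% for the gradual pattern at ρ = 0.7. The article nowhere gives it that role.

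Nor does the article show that the trial will reject too often. It does not say which GEE variance or reference distribution is used. The highest error rate above needs five visits and a trial stopped at 20 patients, and the visits after week 6 are secondary. GEE may also be the branch for skewed data, where the simulated excess at 40 patients is small.

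A condensed article may leave the contrast and the variance correction to an SAP. That is fair for those details. It does not cover what the article does fix: baseline as an outcome level, a model chosen from the data, and adjustment that depends on observed imbalance in a different scale. Analysing to week 6 first and adding follow-up later is ordinary staging and no fault in itself.

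**Conclusion.** The point holds as an improvement available at no cost, not as proof that the analysis is invalid. The stated model can estimate the week-6 change contrast but does not make it, or any week-6 contrast, the deciding test. The omnibus interaction is a poor stand-in: about 83% rejection with an effect at week 3 only, and about 71% power against 84-85% for a baseline-adjusted week-6 comparison under the gradual pattern. The change contrast itself gives up about 11 points to ANCOVA at ρ = 0.5 and about 4 at ρ = 0.7, and practically nothing at 0.9.

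The GEE concern is conditional. Only with an uncorrected sandwich and a z or chi-square reference is three-visit type I error about 6-8% at 40 patients and 8-11% at 20.

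SD, correlation, effect pattern and alpha are all assumptions. The power gap shrinks if the effect appears only at week 6 or if the correlation is very high.

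**What to change.** State one primary test in advance: the active-minus-sham difference in WMFT Functional Ability Scale at week 6, adjusted for baseline Functional Ability Scale in all cases, reported as an estimate with 95% CI. ANCOVA does this; so does the week-6 contrast of a repeated-measures model with baseline as a covariate. If Fugl-Meyer adjustment is wanted, fix it beforehand instead of making it depend on observed imbalance.

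Drop the data-dependent choice between RM-ANOVA and GEE for the primary test, or write down the rule. If GEE is kept, specify a small-sample corrected sandwich with a t or F reference. Label the other visits and the five-visit model as secondary.

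The cost is wording in the analysis section. Baseline and week-6 WMFT are already collected, and no patients, visits or measurements are added.

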**INCLUSION CRITERIA**
18 years or older
Ischemic or hemorrhagic stroke at least 6 months before, confirmed by computed tomography or magnetic resonance imaging
Moderate to severe motor upper limb impairment defined as a score between 7 and 50 in the Fugl-Meyer Assessment of sensorimotor recovery after stroke (0–66) (15)
Ability to provide written informed consent (patient or legal representative)
Ability to comply with the schedule of interventions and evaluations in the protocol

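### Adjustment for baseline severity depends on an undefined observed imbalance, so the primary model is chosen from the data; fix the covariates in advance

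*Protocol article*

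**What the plan says.** The Data Analysis section gives the main model as "Analysis of variance with repeated measures or generalized estimating equations models with factors GROUP (active or sham) and TIME (baseline, 3, 6 weeks"), with the later visits added once follow-up is complete. Severity is not in that model by default. It enters on one condition: "If there is an imbalance in Fugl-Meyer scores between the groups, then the analysis will be adjusted for baseline severity". The article does not say what counts as an imbalance, or when and by whom it is judged.

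Three other places bear on the point.

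- **Table 1, inclusion criteria:** impairment is "defined as a score between 7 and 50 in the Fugl-Meyer Assessment", a wide span on a 0–66 scale.
- **Randomization, Allocation Concealment and Blinding:** patients are allocated "in blocks of four, to active or sham RPSS in a 1:1 ratio". No stratification by severity is described.
- **Sample Size:** the number to recruit is left open, in these terms: "We planned to include up to 40 patients and to determine the final sample size after evaluating the results of the first twenty patients". The primary outcome is given there as "change in WMFT, Functional Ability Scale at 6 weeks compared to baseline".

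No section makes Fugl-Meyer a covariate in all cases.

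**The concern.** A rule of this kind is a two-stage procedure: look at the baseline difference, then pick the model. Three things can go wrong.

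1. If imbalance is undefined, the adjusted and unadjusted results can both be in view when the choice is made.
2. A chance imbalance that is not flagged stays in that trial's estimate if severity predicts the outcome.
3. When the groups look balanced, any precision gained from a prognostic covariate is thrown away, although prognostic strength and not imbalance is the reason to adjust.

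At stake is the credibility of the primary comparison and, depending on how prognostic the baseline measures are, some of the power of a small trial.

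**Working it through.** **No plan figure to reproduce.** The article gives no alpha, power, SD or target difference behind its maximum of 40. It gives only a minimal clinically important difference, "0.2 to 0.4 points for the Functional Ability Scale", and without an SD this cannot be standardised. Below, a two-sided alpha of 0.05, a true effect of 0.6 SD of change and all correlations are assumptions. The 20 per arm follows from 40 patients allocated 1:1.

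**1. How often will the question arise?** The SE of a baseline mean difference, in SD units, is √(2/n).

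- 20 per arm: √(2/20) = 0.316. P(|difference| > 0.25 SD) = 2[1 − Φ(0.25/0.316)] ≈ 43%. Above 0.5 SD: ≈ 11%.
- 10 per arm (the first twenty patients): √(2/10) = 0.447. The same probabilities are ≈ 58% and ≈ 26%.

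**2. What does the planned model test?** Because baseline is a level of TIME, the GROUP × TIME contrast between baseline and 6 weeks compares mean changes. Two things follow.

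- A Fugl-Meyer main effect βX takes the same value at every visit, so it cancels in (6 weeks − baseline). With complete data and a linear model, adding it alone does not alter the contrast; a covariate-by-TIME term is needed.
- The correlation that matters is that of Fugl-Meyer with *change* in WMFT. With equal SDs at both visits,

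  r(change) = (ρ_F6 − ρ_F0) / √[2(1 − ρ_06)],

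  where ρ_F0 and ρ_F6 are the correlations of Fugl-Meyer with WMFT at baseline and 6 weeks, and ρ_06 is the correlation between the two WMFT values. It is zero when Fugl-Meyer tracks WMFT equally well at both visits.

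**3. Type I error** (simulation, 20 per arm, nominal 5%).

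| Procedure | Result |
|---|---|
| Stated rule, imbalance called at baseline p<0.05, r(change) −0.16 to 0.32 | 4.7–5.2% |
| Same rule, r with the analysed outcome 0.3 / 0.5 / 0.7 | 4.8 / 4.3 / 3.7% |
| Always adjusted | about 5% |
| Whichever analysis is significant is kept, r 0.3 / 0.5 / 0.7 | 6.5 / 7.1 / 8.3% |
| Unadjusted test when baseline p is 0.05–0.20, r 0.3 / 0.5 / 0.7 | about 7 / 9 / 12% |
| Same band, r(change) 0 to −0.18 | 4.8–5.8% |

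The band in the last two rows holds 0.20 − 0.05 = 15% of trials. Those rows are conditional rates, not the trial's overall error.

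**4. Power at 0.6 SD of change, 20 per arm.** A change-score test has power ≈ Φ(0.6·√10 − 2.024) = Φ(−0.127) ≈ 45%. The stated rule gave 45–46% in simulation. It rarely adjusts: a p<0.05 trigger fires in 5% of trials.

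For ANCOVA on the 6-week value with both Fugl-Meyer and baseline WMFT:

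- R² = (ρ_F6² + ρ_06² − 2ρ_F6·ρ_06·ρ_F0)/(1 − ρ_F0²)
- variance ratio q = (1 − R²)/[2(1 − ρ_06)]
- power ≈ Φ(0.6·√10/√q/√(1 + 2/35) − 2.028), where √(1 + 2/35) = 1.028 allows for chance imbalance in the two covariates.

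*Lower end*, ρ_F0 = ρ_F6 = 0.7, ρ_06 = 0.9, so r(change) = 0:
R² = (0.49 + 0.81 − 0.882)/0.51 = 0.820; q = 0.180/0.20 = 0.90; power ≈ Φ(1.943 − 2.028) ≈ 47%, a gain of about 2 points.

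*Upper end*, ρ_F0 = 0.5, ρ_F6 = 0.7, ρ_06 = 0.8, so r(change) = 0.2/0.632 = 0.32:
R² = (0.49 + 0.64 − 0.56)/0.75 = 0.76; q = 0.24/0.40 = 0.60; power ≈ Φ(2.382 − 2.028) ≈ 64%, a gain of about 18 points over 45–46%.

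Adding Fugl-Meyer alone to the change-score test moved simulated power by only about −1 to +2 points over r(change) from −0.16 to 0.32. Most of the gain comes from handling baseline WMFT as a covariate together with Fugl-Meyer.

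**5. Cost if the covariates do not help.** With q = 1, power ≈ Φ(1.897/1.028 − 2.028) = Φ(−0.183) ≈ 43% against 45%, a loss of about 2 points. Fugl-Meyer alone costs about 1 point.

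**The case against.** The strongest reply is that the planned analysis already takes out much of the severity effect. With baseline as a level of TIME, the test is close to a comparison of changes, and Fugl-Meyer may be only weakly related to change. A reader who treats the analysis as an unadjusted t-test on the outcome, with correlations of 0.3 to 0.7, could infer a large loss, for instance 46% power against 72% at 0.6 SD when r = 0.7. The documents do not support that reading: it is not the model in the Data Analysis section, and no correlation is reported. This part of the objection stands and sets the size given here.

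A reader might also infer that the rule inflates the false-positive rate. Applied mechanically, it does not; it is neutral or slightly conservative. The 6.5–8.3% figures describe choosing the favourable result, which the article does not propose. The 7–12% figures hold only within one band of baseline p-values and only if Fugl-Meyer predicts what is analysed.

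It can further be said that an article leaves thresholds to a fuller document, that the rule names one covariate and one trigger in advance, and that the trial calls itself preliminary. The missing threshold should indeed carry little weight by itself. But supplying one would still leave a model chosen from the observed data, and that conditional structure is what the article states.

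**Conclusion.** The point holds as a badly fixed rule for the primary analysis. Making adjustment conditional on observed imbalance leaves an avoidable choice between two results, in a trial where the choice will arise often.

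It does not show that overall type I error is inflated: under a mechanical rule the error is about 5% or slightly below. It exceeds 5% only if the choice is made after seeing results, or conditionally on an unflagged imbalance when Fugl-Meyer predicts change in WMFT.

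The power forgone is about nil from Fugl-Meyer alone if that score is weakly related to change. Against an analysis adjusted for both Fugl-Meyer and baseline WMFT it is roughly 2 to 18 points. Those figures rest on 20 per arm, two-sided 5%, an effect of 0.6 SD of change, roughly normal data with equal SDs at both visits, and assumed correlations. A WMFT pre-post correlation close to 1 would remove the gain. The change should be made, but the rule does not invalidate the trial.

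**What to change.** Replace the conditional sentence with:

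> The primary comparison at 6 weeks is adjusted for baseline FMA-UL (continuous) and baseline WMFT in all cases, irrespective of observed balance, by ANCOVA on the 6-week value or by a repeated-measures model of the post-baseline visits with baseline-by-TIME terms. Baseline is then not a level of TIME. The unadjusted GROUP × TIME result is reported as a sensitivity analysis.

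Two details matter. Baseline WMFT cannot be both a level of TIME and a covariate. And a Fugl-Meyer main effect alone, added to the present model, would leave the GROUP × TIME contrast unchanged.

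Both measures are already taken at baseline, so no new data are needed. The cost is a few degrees of freedom: about 1 point of power for Fugl-Meyer if it is not prognostic, and about 2 points in the limiting case where neither covariate helps. The wording should be fixed before any further unblinded results are examined.
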